**Fig. 4 Fig4:**
[figure not shown]
The patients' schedule of trial enrollment, interventions, and assessment. ROM, Range of motion; KSS, Knee society score; WOMAC, Western Ontario and McMaster Universities Osteoarthritis Index; 6MWT, 6-minute walking test; TUG, Timed up and go test. ^*^Both active and passive ROMs of knee flexion and extension will be measured. ^†^Isokinetic strength of knee flexion and extension measured at 60°/sec angular velocity using an isokinetic dynamometer (Systemic 4 Pro, Biodex Medical System, USA). ^‡^ Mixed-type CPM group only

### Primary outcome measurement

#### Range of motion in knee joint

A blinded physiotherapist will measure active and passive ROM in the affected knee joint using a digital inclinometer (Dualer IQ electronic dual inclinometer system; JTECH Medical, UT, USA). Passive ROM will be measured with the patients in the supine, sitting, and prone positions. When evaluating the passive ROM, the assessor will mobilize the knee joint to the end of the range of applied force of 2 kgf using a handheld dynamometer (MicroFET2, Hoggan Health Industries, UT, USA). Active and passive ROM will be evaluated at three time points: the day before the surgery, after the intervention, and 3-months postoperatively.

### Secondary outcome measurement

#### Pain

A numeric rating scale will be used to evaluate the pain of the participants during and at the end of the intervention, and 3-month follow-up. The numeric rating scale is an 11-point parameter for describing the severity of reported pain, ranging from 0 (no pain) to 10 (intractable pain) [15]. Participants will be asked about their average perceived pain intensity in the past day.

### Patients reported outcomes

Patient-reported outcomes will be measured using the Knee Society Score (KSS), Western Ontario and McMaster Universities Osteoarthritis Index (WOMAC), and Kujala Patellofemoral score [16–18].

The KSS is an objective scoring system to assess patient reporting outcomes in osteoarthritis, especially after TKA. The KSS is easy to obtain and concise. The Korean version of the KSS was validated in 2017 by Kim et al. [16], and participants will be assessed using this version.

The WOMAC score was developed by Bellamy et al. [19] and is widely applied to evaluate the status of lower-limb osteoarthritis. The WOMAC questionnaire consists of 24 questions in three domains. Pain (five items), stiffness (two items), and function (17 items) are evaluated on a total scale of 0–100; higher scores indicate greater disability. The Korean version of WOMAC was validated in 2001, and patients will be evaluated using this version [17].

The Kujala patellofemoral score will also be calculated. The Kujala patellofemoral score consists of 13-items with categories related to various levels of functional knee problems. All responses are summed to provide an overall index ranging from 0 to 100 points, with 100 points representing no disability [18].

Satisfaction questionnaires (Additional file 2) will be administered to participants in the mixed-type CPM group at the end of the intervention to compare conventional and new types of CPM machines.

### Swelling

Lower limb swelling after TKAs is a normal response to surgical trauma [20] and may impair postoperative mobilization and the effects of postoperative rehabilitation. Swelling after TKAs was significantly more pronounced in the operated limb and swelling above the knee was more severe than that below the knee [20]. Two randomized trials reported the effect of CPM treatment on the statistically significant reduction in knee swelling after TKAs [21, 22]. We will measure the extent of swelling of the limb through circumference taken 10 cm superior to the upper patellar pole and 10 cm inferior to the lower patellar pole during and at the end of the intervention and 3-month follow-up.

### Gait ability

The Timed Up and Go test (TUG) and 6-minute walking test will be conducted to assess the functional gait ability of the participants. During the TUG test, the patient will be asked to get up from the chair, walk 3 m, return, and sit again. Assessment will be timed during the test. This test has long been used to measure the walking ability of the elderly and is known to be reliable and correlates with the Berg balance test and walking speed [23]. The 6-minute walk test is widely used to assess physical exercise capacity in frailty or sarcopenia in the elderly [24]. The patient will be asked to walk as far as possible along the 30 m corridor for 6 min, and the distance traveled will be measured in meters.

### Isokinetic strength measurement

Knee osteoarthritis can cause weakness of the periarticular skeletal muscles, mainly in the knee extension group. This weakness of knee extension slows the gait speed of the patients, and therefore, is an important indicator of gait [25]. After TKA, isokinetic measurements using an isokinetic dynamometer are known to be reliable, easy to perform, accurate, and safe [26]. Peak torques of the knee flexors and extensors of both sides will be measured during concentric contraction at 60°/sec angular velocity using an isokinetic dynamometer (Systemic 4 Pro; Biodex Medical System, New York, NY, USA).

### Sample size calculation

The sample size was calculated based on the data of a preliminary pilot study conducted by our group. The number of participants in the pilot study was 16 (conventional CPM group: 6, sitting-type CPM group: 6, mixed-type CPM group: 4). The primary hypothesis was that there would be a significant difference in the passive ROM before and after treatment between the groups. The means ± standard deviations of passive ROM of the knee joint after treatment were 105.2±14.7, 100.0±26.5, 92.5±8.9 in conventional CPM group, sitting type CPM group, and mixed-type CPM groups respectively, in the preliminary pilot study.

Thirty-five people per group were required for a significance level of 5% (a significance level of 0.05/4 × 100% of each hypothesis) and 80% statistical power. Assuming an expected dropout rate of 20%, at least 42 participants per group will be required.

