**Methods:**

This study presents the protocol of a prospective, multicenter, single-blinded, three-armed randomized controlled trial (RCT). One hundred and twenty-six patients receiving unilateral TKAs will be recruited at the physical medicine and rehabilitation clinics of two urban tertiary medical hospitals. The patients were randomly divided into three groups with a 1:1:1 allocation. The intervention group will receive two weeks of post-operative rehabilitation using a new type of CPM machine. The control group will receive 2 weeks of post-operative rehabilitation using conventional CPM machines. The third group will receive post-operative rehabilitation with both types of CPM machines. The primary outcome will be the change in the passive ROM of the affected knee joint from baseline to 2 weeks after baseline assessment. The secondary outcomes will be pain and functional measurements, and will include patient-reported outcomes and performance tests surveyed at multiple time points up to 3 months after TKA.

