**Fig. 1 Fig1:**
[figure not shown]
A new type of CPM machine (Resilion K20P®, HEXAR humancare, Korea) will be used in this randomized trial

We hypothesized that the efficacy of CPM machines in patients receiving TKRs differed according to the position of the patients and that CPM machines applied in the sitting position of patients would be more effective than conventional methods of CPM treatment. Therefore, the purpose of this study was to compare the effect of conventional CPM and CPM treatments applied in the sitting position in patients receiving TKAs and to establish a more suitable rehabilitation strategy using a CPM machine.

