#### Randomization, allocation, and blinding

Orthopedic surgeons perform an initial screening of all patients who visit the department of orthopedic surgery due to degenerative knee OA. If the patients fulfill the eligibility criteria, they are referred to the principal study coordinator. The principal study coordinator performs the final eligibility assessment and asks for informed consent to enroll in this study. After their consent is obtained, participants are randomly assigned to each group in a 1:1:1 ratio to the conventional type, mixed type, and sitting type CPM groups. Block randomization will be used on groups of 12 to balance relocation into the intervention groups. After the initial allocation, the mixed CPM groups will be re-allocated into two groups. Mixed groups will receive combined interventions with two types of CPM machines and consist of two subgroups. One of the subgroups will receive intervention using the conventional type of CPM, followed by the sitting type of CPM, and the other subgroup will recieve intervention in the opposite order. This trial will be blinded to the assessor; after randomization, the allocation of participants will be confidentially managed by the principal study coordinator. All assessments will be conducted by a single trained physiotherapist in each hospital who is experienced in post-operative rehabilitation treatment and will be blinded to group allocation. Due to the nature of the study, participants will not be blinded and will be instructed not to communicate with any other researcher or physiotherapists about their interventions to minimize potential bias. If participants would like to discuss their rehabilitation program during the intervention, they will be able to do so with the unlabeled study coordinator.

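### The primary hypothesis is any passive ROM difference among three arms, so a mixed-arm difference alone can meet it and leave sitting versus conventional CPM unanswered

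*Protocol article*

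**What the plan says.** Under Randomization, allocation, and blinding, "participants are randomly assigned to each group in a 1:1:1 ratio to the conventional type, mixed type, and sitting type CPM groups". The Abstract calls the sitting arm the intervention and the conventional arm the control, then adds: "The third group will receive post-operative rehabilitation with both types of CPM machines".

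The last paragraph of the Background gives the aim: "the purpose of this study was to compare the effect of conventional CPM and CPM treatments applied in the sitting position". The expectation stated there is that "CPM machines applied in the sitting position of patients would be more effective than conventional methods of CPM treatment". The Discussion also describes the trial as a comparison of the conventional and sitting types.

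Sample size calculation states the hypothesis to be tested: "The primary hypothesis was that there would be a significant difference in the passive ROM before and after treatment between the groups". It sets "a significance level of 5% (a significance level of 0.05/4 × 100% of each hypothesis", with 80% power and 35 per group, but does not say what the hypotheses are. Statistical analysis gives a 5% level. It describes a model for the secondary outcomes whose group factor has two levels, intervention and control, so the mixed arm has no place in it.

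**The concern.** The purpose concerns two arms and the primary hypothesis concerns three. Three arms give three pairwise contrasts: sitting–conventional, mixed–conventional and mixed–sitting. The hypothesis as worded is met when any of them differs. Only the first answers the question in the Background.

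The division by four implies several tests, but the article does not say which of them decides the trial. The number four does not identify them either, since there are three pairwise contrasts. The trial could therefore report its primary hypothesis as confirmed because the mixed arm did worse or better, with nothing established about sitting against conventional CPM. The pilot makes this a practical risk, because its largest gap is between conventional and mixed.

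**Working it through.** **Inputs** (Sample size calculation). Pilot passive ROM after treatment: "105.2±14.7, 100.0±26.5, 92.5±8.9 in conventional CPM group, sitting type CPM group, and mixed-type CPM groups respectively". Pilot sizes: "conventional CPM group: 6, sitting-type CPM group: 6, mixed-type CPM group: 4". Planned evaluable number: 35 per group. Level per hypothesis: 0.05/4 = 0.0125. Tests are taken as two-sided, because the article does not say.

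**1. The plan's own figure.** No test at 0.0125 gives 35 per group from the pilot values. The pairwise tests need 379 (conventional–sitting), 21 to 23 (conventional–mixed) and 155 to 186 (sitting–mixed). A three-group ANOVA with a common SD needs 56 to 70. The nearest match is a simulated F test with arm-specific SDs at an undivided 0.05, which needs about 33. The figure of 35 therefore does not show which contrast was meant. Whether 35 is right is a separate matter.

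**2. Each pairwise test at 35 per arm.** Standard error = √((SD₁² + SD₂²)/35).

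| Contrast | Gap (degrees) | Standard error | Gap/SE | Power at 0.0125 |
|---|---|---|---|---|
| Conventional–mixed | 105.2 − 92.5 = 12.7 | √((14.7² + 8.9²)/35) = 2.90 | 4.37 | about 96% |
| Sitting–mixed | 100.0 − 92.5 = 7.5 | √((26.5² + 8.9²)/35) = 4.73 | 1.59 | about 17% |
| Conventional–sitting | 105.2 − 100.0 = 5.2 | √((14.7² + 26.5²)/35) = 5.12 | 1.02 | about 7% |

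**3. The three tests together** (simulated normal data, pilot values as truth). At 0.0125 at least one pairwise test is significant in about 96 to 97% of trials. In about 93% of those, conventional–sitting is not significant.

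**4. A three-group F test, if that is what is meant.** It rejects in about 58% of trials at 0.0125 and about 83% at 0.05. Sitting–conventional, tested at the same level, is not significant in about 89% and 80% of those rejections.

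**5. Sensitivity to the pilot SDs.** The pooled SD is √((5×14.7² + 5×26.5² + 3×8.9²)/13) = 19.3. With this SD in every arm, the F test at 0.05 rejects in about 68% of trials, and 72% of those lack a significant sitting–conventional difference. If sitting equals conventional and only the mixed arm is 12.7 degrees lower, it rejects in about 81%, and 94% of those lack it.

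**6. Power for the contrast of interest.** The average-variance SD is √((14.7² + 26.5²)/2) = 21.4.
- At the pilot gap of 5.2 degrees, 35 per group gives about 17% power at 0.05 and 7% at 0.0125.
- Required n per group = 2(z₁₋α/₂ + z₀.₈)² × SD²/gap². At 0.05 this is 2 × 2.802² × 459.2/27.04 ≈ 267. At 0.0125 it is 2 × 3.339² × 459.2/27.04 ≈ 379.
- With 35 per group, 80% power by the t test needs a gap of 0.68 SD at 0.05 (0.68 × 21.4 ≈ 14.6 degrees) or 0.82 SD at 0.0125 (0.82 × 21.4 ≈ 17.5 degrees).

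**The case against.** The strongest defence is that the intended contrast is clear enough. The Background, Abstract and Discussion all point to sitting versus conventional, and a list of hypotheses with their testing order is commonly left to an analysis plan that is not shown. The first half stands as a description of intent, and the missing list is not in itself the point. But the article does fix a primary hypothesis, and the one it fixes is wider than that intent.

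Three stronger readings are tempting and are not supported:

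- A reader might infer that the three comparisons inflate the false-positive rate. They would if each were read at 5%. The article states 0.05/4 for each hypothesis, and three pairwise tests at that level give a family-wise rate of about 0.03.
- A reader might fault a non-directional test of a directional expectation. A two-sided test of such an expectation is ordinary practice, and the fix below is two-sided too.
- A reader might infer from the pilot values that the hypothesis wording is why sitting would almost never be shown superior. That follows from pilot means that favour conventional CPM, and renaming the primary contrast would not change it.

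It is also fair to object that the article assigns no F test to the primary outcome; one-way ANOVA appears there only for baseline values. The F-test figures are therefore conditional, and the pairwise figures at 0.05/4 are closer to the text.

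**Conclusion.** The point holds as a mismatch between the stated primary hypothesis and the stated purpose. It follows from the wording alone and does not depend on the simulation. On the pilot values the usual route to a significant result is conventional versus mixed, and about 93% of the trials with any significant pairwise result at 0.05/4 would not have the sitting–conventional result among them.

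The percentages are illustrative. They rest on 4 to 6 patients per arm, on post-treatment values where the hypothesis concerns change (whose SD is not given), on normal data and on two-sided tests. With a common SD the rejection rates are lower, but the pattern is the same. The documents do not show that the error rate is uncontrolled, nor that the investigators intend to claim success on a mixed-arm difference. The wording merely allows that claim. It should be corrected before the outcome data are analysed.

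**What to change.** In Sample size calculation and Statistical analysis:

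- Name sitting minus conventional in the primary passive ROM change as the single deciding contrast, tested two-sided and reported with its confidence interval.
- State its alpha, and reconcile the 0.05/4 in one section with the 5% in the other.
- Test mixed versus conventional and then mixed versus sitting in that fixed order, only if the first contrast is significant. Otherwise label both exploratory.
- Restate the power for the named contrast at 35 per group, with the gap it can detect, and do not carry over the 80%.

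The change itself is wording and needs no new data. Trial status reports 68 patients recruited with recruitment still open, and Data management rules out an interim analysis, so it can be made as a dated amendment before any results are analysed. It has two costs. A difference involving only the mixed arm no longer counts as success, and the stated power becomes less favourable: about 17% at 0.05 or 7% at 0.0125 if the gap is the pilot's 5.2 degrees. That weakness is already present, and the three-arm wording hides it.

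### If the 0.05/4 split in the sample size section is also the final testing rule, Holm's procedure on the same four hypotheses would keep the 5% familywise error and recover a modest amount of power

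*Protocol article*

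**What the plan says.** The protocol article describes a "single-blinded, three-armed randomized controlled trial (RCT". Under Sample size calculation it plans at "a significance level of 5% (a significance level of 0.05/4 × 100% of each hypothesis" and "80% statistical power", and concludes that "Thirty-five people per group were required". This is the only place where the document divides the significance level.

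The same section states one hypothesis in words: "The primary hypothesis was that there would be a significant difference in the passive ROM before and after treatment between the groups". It does not say which four hypotheses share the 5%. The section on outcome measurement and timeline names two primary time points, the end of the intervention and 3 months, whereas the abstract names one, at 2 weeks. The Statistical analysis section sets a 5% level and names no multiplicity procedure.

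**The concern.** A plain Bonferroni rule holds every hypothesis to the same strict threshold whatever happens to the others. Holm's procedure starts at that threshold and relaxes it after each rejection, with the same bound on the familywise error. It needs no assumption about how the tests are correlated, and it is no less valid for one choice of four hypotheses than for another. A trial that tests each hypothesis at a fixed 1.25% therefore gives something away and gets no extra protection in return.

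What is at stake is power, not validity. The comparison of sitting with conventional CPM, which the Background gives as the purpose of the trial, would be held to 1.25% even after other hypotheses had been rejected. In a trial of 126 patients, power that costs no patients is worth having.

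**Working it through.** **Inputs.** From the sample size section: familywise level 0.05 over four hypotheses, power 80%, 35 per group before dropout, pilot results "105.2±14.7, 100.0±26.5, 92.5±8.9 in conventional CPM group, sitting type CPM group, and mixed-type CPM groups respectively" and pilot sizes "conventional CPM group: 6, sitting-type CPM group: 6, mixed-type CPM group: 4". Two-sided tests are assumed, because the document does not state sidedness.

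**1. The split is valid.** 0.05/4 = 0.0125, and 4 × 0.0125 = 0.05. If the four tests were independent, the familywise error would be 1 − (1 − 0.0125)^4 = 0.0491.

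**2. The plan's own figure.** n per group = 2 × (z for 1 − α/2 + z for 80%)² × (SD/difference)². At α = 0.0125 the z-values sum to 2.498 + 0.842 = 3.340. The first SD in each row is pooled over the pair, the second over all three arms.

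| Pair | Difference | SD | n per group |
|---|---|---|---|
| Conventional vs sitting | 5.2 | 21.43 / 19.27 | 379 / 307 |
| Sitting vs mixed | 7.5 | 21.65 / 19.27 | 186 / 148 |
| Conventional vs mixed | 12.7 | 12.84 / 19.27 | 23 / 52 |

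None of these gives 35. The effect used below is therefore back-solved from 35 per group: 3.340 × √(2/35) = 0.80 SD. It is an assumption. For conventional versus sitting the pilot gives 5.2/21.43 = 0.24 SD. The pilot figures are post-treatment values and no SD of change is given, so a calculation on change could differ.

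**3. Why Holm never does worse.** Holm orders the four p-values and compares them in turn with 0.05/4 = 0.0125, 0.05/3 = 0.0167, 0.05/2 = 0.025 and 0.05, stopping at the first failure. No threshold is below 0.0125, so every p-value that passes Bonferroni also passes Holm. For the familywise error, suppose m of the four nulls are true. The first true null to be tested meets a threshold of at most 0.05/m, so the chance of any false rejection is at most m × 0.05/m = 0.05, whatever the correlation.

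**4. Size of the gain, general case.** Average power per false null at 35 per group and 0.80 SD, with correlation between tests of 0 to 0.5 (normal approximation, 400,000 draws):

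| Nulls that are false | Bonferroni 0.05/4 | Holm |
|---|---|---|
| 1 | 80% | 80.1–80.2% |
| 2 | 80% | 82.0–82.3% |
| 3 | 80% | 84.4–85.3% |
| 4 | 80% | 87.5–89.4% |

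With all four false, the chance of rejecting all four rises from 41–56% to 69–76%. The chance of finding at least one real effect does not change (99.8% under both rules at correlation 0, 96.7% under both at 0.5), because the first step is the same.

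**5. Size of the gain if the family is the overall test plus three pairs.** Simulated with t and F tests, equal SDs and 0.80 SD between sitting and conventional, power for that pair is 78% with Bonferroni. With Holm it is 79% if the mixed arm lies midway and 83% if the mixed arm equals one of the others. In this family, one differing pair makes the overall null false and forces at least one other pair to differ, so the single-false-null row of step 4 cannot arise. It can arise in other families of four.

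**6. On the raw pilot figures.** At 35 per group, conventional versus sitting has 7–9% power at 1.25% and 17–20% at an unsplit 5%. Holm's most generous step is 5%, so it cannot exceed the second range.

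**7. Sample size.** Holm's first step is 0.0125, so planning at 0.0125 suits a Holm analysis and 35 stands as the planning number.

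**The case against.** The strongest reply is that the document does not fix a single-step rule for the final tests. The split appears only in the sample size calculation, the analysis section says 5%, and an unseen analysis plan may already name a step-down procedure. That stands, and it makes the loss conditional. A reader might infer that the trial is certain to lose power; the documents do not show this. They do leave the only stated multiplicity rule at odds with the unsplit 5%, and one sentence would settle it.

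It is also fair that Bonferroni is valid and that the gain is small. Both points stand, and this is a matter of efficiency.

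Three stronger readings are tempting.

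- **A closed test (overall test at 5%, then pairs at 5%).** This assumes that the family is the overall test plus three pairs at one time point, but the family is not listed and the Methods name two primary time points. Run at 5% at both, its familywise error under the full null is 8.4–9.6%. It also leans on equal SDs, while the pilot's run from 8.9 to 26.5. With those SDs the overall F test rejects about 6% of the time under the full null. With a three-arm pooled error term, sitting versus conventional is falsely rejected nearly 10% of the time when only the mixed arm differs (5.1% if only the two arms compared are pooled). That last fault would also reach Holm if it were fed p-values from the three-arm pooled term, since Holm presumes valid p-values.
- **A fixed sequence with sitting versus conventional first.** The sample size section ranks no contrast first.
- **A smaller sample.** With all four nulls false, 29–30 per group would give 80% average power under Holm. With only one false, 35 is still needed.

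**Conclusion.** The point holds as a conditional, low-cost improvement. If 0.05/4 is applied as a fixed threshold to each hypothesis, Holm on the same four p-values is at least as powerful in every case, at the same 5% familywise error. That part needs only valid p-values and no knowledge of what the four hypotheses are.

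The size depends on how many nulls are false and on the back-solved 0.80 SD, and it runs from almost nothing to 7–9 points per hypothesis. The figure of 1 to 5 points for the main comparison also rests on a guessed family and equal SDs. The change does not rescue that comparison if the pilot values are near the truth.

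**What to change.** Keep 0.05/4 as the planning level in the sample size section, and say that it is the first step of Holm's procedure. In both that section and Statistical analysis, state that the four primary hypotheses, named there, will be tested with Holm's procedure at a familywise 5%. Pairwise p-values should come from the two arms compared, given how far the pilot SDs differ.

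The cost is one sentence in each section and no extra patients. Intervals that match a step-down test are less simple, so unadjusted intervals could be shown beside adjusted p-values. Recruitment is under way (68 patients when the article was written) and no intermediate analysis is planned, so the rule can be set before outcomes are analysed. The sponsor should check whether the change counts as significant under the notification commitment in the ethics section.

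### The dropout allowance is miscalculated: at 20% dropout, 42 per group leaves an expected 33.6 evaluable patients, slightly short of the 35 the plan requires (minor)

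*Protocol article*

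**What the plan says.** The section Sample size calculation gives the requirement before losses: "Thirty-five people per group were required for a significance level of 5% (a significance level of 0.05/4 × 100% of each hypothesis"), together with "80% statistical power". The next sentence adds the allowance for losses: "Assuming an expected dropout rate of 20%, at least 42 participants per group will be required".

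The Methods paragraph of the abstract carries this into the recruitment target: "One hundred and twenty-six patients receiving unilateral TKAs will be recruited". Allocation there is 1:1:1 to three groups, so 126 is 3 × 42.

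The article gives no other dropout rate, and nowhere defines the 20% as a share of the evaluable number instead of the enrolled number.

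**The concern.** The plan enlarges the sample for one purpose: to have 35 patients per group left after the expected losses. Adding 20% to 35 does not achieve this, because the 20% loss then applies to the larger enrolled number. Twenty percent of 42 is 8.4 patients, while only 7 were added.

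What is at stake is the consistency of the trial's headline number. The article presents 42 per group as a sufficient minimum at 20% dropout. On its own figures it is not sufficient, so the stated power is not secured at the stated dropout rate.

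**Working it through.** **Inputs.** From Sample size calculation: 35 evaluable per group, 20% dropout, 42 enrolled per group, 80% power, and 0.05/4 = 0.0125 per hypothesis. From the abstract: 126 in total, three equal groups.

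**1. Reproduce the plan's figure.** n × (1 + d) = 35 × 1.20 = 42 exactly, and 3 × 42 = 126. So the stated number comes from multiplying by 1.20.

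**2. Correct allowance.** n / (1 − d) = 35 / 0.80 = 43.75, rounded up to 44 per group; 3 × 44 = 132. Check: 44 × 0.80 = 35.2, which is at least 35. Rounding cannot turn 43.75 into 42, and 43 is also too few: 43 × 0.80 = 34.4.

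**3. What 42 delivers at 20% dropout.**

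| | Enrolled | Expected evaluable | Required | Shortfall |
|---|---|---|---|---|
| Per group | 42 | 42 × 0.80 = 33.6 | 35 | 1.4 |
| Total | 126 | 126 × 0.80 = 100.8 | 105 | 4.2 |

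The gap in enrolment is a different quantity: 44 − 42 = 2 per group, or 132 − 126 = 6 in total.

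**4. Dropout that 42 can bear.** 1 − 35/42 = 0.167. So 42 per group keeps 35 evaluable up to 16.7% dropout.

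**5. Illustration of the power lost.** The section names neither the test nor its sidedness. Assume a two-sided two-group t test, and fix the standardised difference so that 35 per group gives exactly 80%. That difference is 0.817 at alpha 0.0125 and 0.679 at alpha 0.05.

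| Evaluable per group | Power, alpha 0.0125 | Power, alpha 0.05 |
|---|---|---|
| 35 | 80.0% | 80.0% |
| 34 | 78.6% | 78.8% |
| 33.6 (expected) | 78.0% | 78.3% |
| 33 | 77.0% | 77.6% |

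A three-group analysis of variance calibrated in the same way gives 76.8% to 78.5% at alpha 0.0125 and 77.4% to 78.7% at alpha 0.05, for 33 to 34 per group. The loss is about 1 to 3 percentage points in every case.

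**The case against.** The strongest reply is that this hardly matters. An expected shortfall of 1.4 patients per group and about 2 points of power changes no design decision, analysis or interpretation. That is right about the size, and it is why the point is minor. It does not make the sentence correct.

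A second reply is that the shortfall is conditional: it arises only if dropout exceeds 16.7%. The article also calls 42 a minimum, so more could be enrolled. Both are true, but 20% is the plan's own assumption, and the abstract fixes the target at 126.

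A third reply is that the Statistical analysis section plans an intention-to-treat analysis with the handling of missing data still to be decided, so a patient who drops out may still contribute information. This stands in part: 33.6 is a complete-case count, not a certain loss of information. It does not justify 42, because the plan itself enlarges the sample in order to protect 35.

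A reader might go further and infer that the trial is materially underpowered, or that its true power is 77%. The documents support neither. The 77% belongs to 33 patients per group, which is 33.6 rounded down; at the expected number it is 78%. More importantly, every power figure above takes for granted that 35 per group gives 80%. That could not be confirmed from the pilot summaries ("105.2±14.7, 100.0±26.5, 92.5±8.9 in conventional CPM group, sitting type CPM group, and mixed-type CPM groups respectively"). With those values, two-sided pairwise comparisons at 0.0125 need 21, 155 or 379 per group, depending on the pair. A one-way analysis of variance needs 41 to 45 at 0.05 and 56 to 63 at 0.0125. The summaries are post-treatment values and no standard deviation of change is given, so this does not show that 35 is wrong. It does mean that the actual power at 33 or 34 per group is unknown.

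**Conclusion.** The sentence is wrong as written, and the error is minor. The plan multiplied by 1.20 where it should have divided by 0.80. Its three figures, 42 enrolled, 20% dropout and 35 evaluable, are mutually inconsistent, and the total of 126 inherits the fault.

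This conclusion rests on two things only: that 35 is the plan's own stated requirement, taken here at face value, and that a dropout rate is a share of those enrolled. It does not depend on the test, the alpha or the origin of the 35. The power range of about 77% to 79% does depend on them and serves only to show the scale.

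**What to change.** Restate the sentence in Sample size calculation to say that 42 per group (126 in total) keeps 35 evaluable per group only if dropout is at most 16.7%, and that at 20% dropout about 33 to 34 per group remain, slightly below the number required for 80% power. This costs one sentence and no extra patients.

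Do not insert a power figure unconditionally. If one is wanted, state the test, its sidedness and the assumption that 35 per group gives 80%.

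If the sponsor prefers to keep both the 20% dropout and the 35 evaluable, the arithmetically consistent plan is 44 per group, 132 in total, and the total in the abstract changes with it. That costs six more patients. The Trial status section reports 68 recruited with recruitment still open, so either course was available when the article was written.
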